### Study subjects

Married women of reproductive age (MWRA), who are residing in selected villages of Mirpur Sakro and willing to participate will be included in the study.

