### Sample size

Multistage sampling technique will be used to recruit the participants (Fig. 1). According to our best knowledge, we could not find any studies conducted to determine the mobile phone usage and willingness among women to receive SMS text message–based mHealth interventions to improve ANC services in Pakistan, although the mobile phone access in Pakistani women is 39.2%, according to Pakistan demographic and health survey (PDHS) [8]. Therefore, we assumed that 50% of women use mobile phone and are willing to receive voice-message based mHealth intervention for improving ANC services. The maximum sample size is 384, which was calculated using the proportion of women who have mobile phone and are willing to receive voice-message based mHealth intervention for improving ANC services. Considering a 10% nonresponse rate, we calculated the final sample size to be 415. A non-probability purposive sampling will be used to select 415 MWRA, from the households due to lack of availability of household line listing. From each of the 20 villages, households will be selected using proportionate sampling to complete sample size of 415. From beach household, one women will be randomly selected for the purpose of this survey.

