### Data collection methodology

Epicollect will be used to collect data from 415 women. Epicollect5 is a free web-based tool that enables to collect customized data (including location and media) using a mobile device. The data collection form will be created on the Epicollect 5 app, which can be opened on smartphone by a data collector to collect data in the field (either online or offline). The real-time data can be viewed and downloaded on excel sheet for analysis. Three data collectors will be hired and trained for data collection. One week training of data collectors will be conducted to brief them about study goals and objectives, research ethics (taking informed consent), study questionnaire and use of Epicollect 5 app. The PI and field supervisor will monitor the field activities to ensure the transparency and quality of data collection. Quality of data will also assessed through random checks by the principal Investigator.

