### Data analysis

Data will be analyzed using IBM SPSS Statistics version 23, with a level of significance as < 0.05
Descriptive: Frequencies, means, and SD will be calculated to describe the variables. Demographic and mobile phone usage data will be compared between respondents belonging to different villages.Inferential: Chi-square and binary logistic regression models will be used to identify factors associated with willingness to use mobile phones for improving antenatal care attendance. Multiple logistic regression will be performed to determine adjusted odds ratio (AOR) for the willingness to use mobile phones for antenatal care attendance; the adjusted variables included residence, ability to read, ownership of mobile phone, routine use of mobile, age group, and duration of mobile phone use.

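### The final sample size of 415 does not follow from 384 and 10% nonresponse, and the article does not settle whether 415 counts women approached or women interviewed

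*Protocol article*

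**What the plan says.** The Sample size section assumes a proportion of one half: "we assumed that 50% of women use mobile phone and are willing to receive voice-message based mHealth intervention". It then gives the base number: "The maximum sample size is 384, which was calculated using the proportion of women who have mobile phone and are willing to receive" the messages. The allowance and the total follow in one sentence: "Considering a 10% nonresponse rate, we calculated the final sample size to be 415". No margin of error is stated.

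Elsewhere 415 is described as the number of women who provide data. The Data collection methodology section says "Epicollect will be used to collect data from 415 women", and the Methods part of the abstract says the same and speaks of recruiting 415 participants. Later in the Sample size section, "households will be selected using proportionate sampling to complete sample size of 415". The Study subjects section limits the study to women "who are residing in selected villages of Mirpur Sakro and willing to participate will be included in the study". The article does not say whether women who decline are replaced.

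**The concern.** The section gives a base, a nonresponse rate and a result, with one arithmetic step between them. A reader who takes that step does not reach 415. This is the only sample-size derivation in the article, and 415 is the number the fieldwork is built around, so the stated basis for it should be correct.

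The second issue is what 415 counts. A number enlarged for nonresponse is normally the number to approach, and the completed interviews are expected to be fewer. A number of women from whom data are collected is the number completed. The article uses 415 for both. How many interviews to expect, and so what precision to expect, depends on which is meant.

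**Working it through.** **Inputs.** From the Sample size section: assumed proportion p = 0.50, base 384, nonresponse 10%, final 415. From the Data analysis section: "with a level of significance as < 0.05", taken here as two-sided 95% confidence (z = 1.96). The half-width d = 0.05 is an assumption, because the article states none.

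**Step 1: the base of 384.** n = z² p(1 − p)/d² = 1.96² × 0.25/0.05² = 384.2. This reproduces the stated 384, which supports d = 0.05 as the likely target but does not prove it.

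**Step 2: the inflation for 10% nonresponse.**

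| Method | Calculation | Total | 415 falls short by |
|---|---|---|---|
| Divide by the response rate | 384/0.90 = 426.7 | 427 | 12 (12/415 = 2.9%) |
| Add 10% | 384 × 1.10 = 422.4 | 423 | 8 (8/415 = 1.9%) |

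Neither method gives 415.

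**Step 3: the allowance that 415 contains.** As nonresponse: 1 − 384/415 = 7.5%. As an add-on: 415/384 − 1 = 8.1%. In women, 415 − 384 = 31 are added where 427 − 384 = 43 (or 423 − 384 = 39) would be needed.

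**Step 4: what each meaning of 415 implies.** Half-width = 1.96 × √(0.25/n), under simple random sampling at p = 0.5.

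| Case | Interviews | Against 384 | Half-width (points) |
|---|---|---|---|
| Base as calculated | 384 | 0 | 5.00 |
| 415 approached, 10% do not respond, no replacement | 415 × 0.90 = 373.5 | about 10 fewer (10.5/384 = 2.7%) | 5.07 |
| 415 completed interviews | 415 | 31 more | 4.81 |

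**The case against.** A reader might infer that the survey will end with fewer interviews than it needs. The article does not support that. A shortfall requires three things together: 415 is the number approached, a full 10% do not respond, and nobody is replaced. The article states the 10% as a planning rate but neither of the other two. Most of its text leans the other way: data are collected from 415 women, households are selected until 415 is complete, and only willing women are study subjects, so those who refuse would not be among the 415. On that reading 384 is exceeded. The article also calls 384 a maximum, the largest requirement over possible proportions, and sets no minimum number of completed interviews. This objection stands in full.

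It can also be said that the discrepancy is trivial. The gap is under 3% of 415 by either method, and the worst case costs 0.07 percentage points of half-width. Villages and women are selected purposively, so a simple-random-sampling margin does not describe the survey's real uncertainty in any case. This stands as a statement about impact. It does not make the sentence correct, because the inputs are given and only one step separates them from the result.

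A last defence is a finite-population correction that was not reported. With about 20,000 women, 384.1/(1 + 383.1/20,000) = 376.9, and 376.9 × 1.10 = 414.6, which rounds to 415. But the article states no such population and inflates from 384. If this was the route, the base should read 377, and the sentence would still need correcting.

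**Conclusion.** The point holds as a minor error that is wrong as written. From 384 and 10% nonresponse the total is 427, or 423 by the multiplicative method. The stated 415 provides about 7.5% nonresponse, or an 8.1% add-on. This depends only on figures in the Sample size section. Separately, the article uses 415 both as a number enlarged for nonresponse and as the number of women giving data, and does not reconcile the two.

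The consequence for precision is conditional and small: at worst about 373 interviews and 5.07 instead of 5.00 points, given the assumed d = 0.05 and the three conditions above; at best 31 interviews more than 384 and 4.81 points. It would be going too far to say that the planning figure fails on either meaning. If 415 are completed interviews, the calculated 384 is met and only the description of the allowance is faulty. No planned analysis is affected.

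**What to change.** Correct the sentence in the Sample size section in one of two ways:

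- Keep 415 and restate the allowance as about 7.5% nonresponse on 384.
- Keep the 10% and restate the total as 427 women approached to yield 384 interviews (423 if the multiplicative method is intended).

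Then say once whether 415, or its replacement, means women approached or women interviewed, and use it in that sense in the abstract, the Sample size section and the Data collection methodology section. If 415 is meant as completed interviews, say so and give the number to approach at 10% nonresponse: 415/0.90 = 461.1, so 462.

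The first option costs one corrected sentence and no extra fieldwork. The second means approaching 12 more women than 415 (8 if multiplicative).

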**Fig. 1 Fig1:**
[figure not shown]
Sampling technique

### Data collection tool

A structured questionnaire will be designed to assess mobile phone access, usage and willingness among women to receive voice-based mHealth intervention to improve ANC services. The survey instrument will be developed in English, which will be underwent forward and backward translation to ensure semantic consistency (English to Sindhi then English). The instrument will be in three main sections such as: Socio-demographic characteristics, ownership, knowledge and usage of mobile phone and willingness for receiving voice message for antenatal care attendance. Before the data collection, a pilot testing of questionnaire will be conducted on fifty women), belonging to other talkuka. The necessary modifications will be made on the basis of pretest findings.

### Data collection methodology

Epicollect will be used to collect data from 415 women. Epicollect5 is a free web-based tool that enables to collect customized data (including location and media) using a mobile device. The data collection form will be created on the Epicollect 5 app, which can be opened on smartphone by a data collector to collect data in the field (either online or offline). The real-time data can be viewed and downloaded on excel sheet for analysis. Three data collectors will be hired and trained for data collection. One week training of data collectors will be conducted to brief them about study goals and objectives, research ethics (taking informed consent), study questionnaire and use of Epicollect 5 app. The PI and field supervisor will monitor the field activities to ensure the transparency and quality of data collection. Quality of data will also assessed through random checks by the principal Investigator.

### Ethical considerations

Consent of participation & publication will be taken from the study participants.Ethical approval has been taken from Aga Khan University Ethical Review CommitteeParticipants will be assured that the given information will be kept confidential and only be used for research purpose.

### Data analysis

Data will be analyzed using IBM SPSS Statistics version 23, with a level of significance as < 0.05
Descriptive: Frequencies, means, and SD will be calculated to describe the variables. Demographic and mobile phone usage data will be compared between respondents belonging to different villages.Inferential: Chi-square and binary logistic regression models will be used to identify factors associated with willingness to use mobile phones for improving antenatal care attendance. Multiple logistic regression will be performed to determine adjusted odds ratio (AOR) for the willingness to use mobile phones for antenatal care attendance; the adjusted variables included residence, ability to read, ownership of mobile phone, routine use of mobile, age group, and duration of mobile phone use.

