### Study setting

Thatta district of Sindh province, lies at the coast of Arabian Sea and is situated about 100 km from the city of Karachi. The total population of district Thatta is about 1 million, which is primarily a rural area (82%). Most people of Thatta speak Sindhi language (87%). About 76% of the population are concentrated in two talukas (sub-districts, Thatta and Mirpur Sakro) of the total of four talukas in the district. The study will be conducted in Mirpur Sakro taluka of district thatta, where Community Health Sciences Department of Aga Khan University has recently established a Rural Health Program (RHP). Mirpur Sakro, is the second biggest taluka of the district in terms of population and has 14 union councils, and 2 town committees. The RHP program is running in 125 villages. The data will be collected from 20 purposively selected villages out of 125 villages. The villages have been divided into three stratas, based on their road distance from health facility (Taulka hospital). The three strata are defined as follows: (i) Villages situated less than 5kms from the health facility (ii) Villages that are 5-10kms away and; (iii) Villages that are more than 10kms away from the health facility.

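### The planned chi-square and logistic analyses ignore clustering of women within 20 villages, so precision is overstated for factors that vary by village and for any prevalence interval

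*Protocol article*

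**What the plan says.** On the sample, the Sample size section states: "Multistage sampling technique will be used to recruit the participants". The first stage is set under Study setting: "The data will be collected from 20 purposively selected villages out of 125 villages". These villages are grouped into three bands by road distance to the taluka hospital. The second stage is under Sample size: "From each of the 20 villages, households will be selected using proportionate sampling to complete sample size of 415". One woman is taken per household, so there is no clustering within households, and the village is the cluster.

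On the analysis, the Data analysis section states: "Data will be analyzed using IBM SPSS Statistics version 23, with a level of significance as < 0.05", and then "Chi-square and binary logistic regression models will be used to identify factors associated with willingness to use mobile phones for improving antenatal care attendance". A multiple logistic model follows, adjusted for residence, literacy, phone ownership, routine phone use, age group and length of phone use.

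The article nowhere mentions clustering, an ICC, a design effect, a village random effect, GEE, robust variance or a complex-samples procedure. Residence is not defined, and it is not described as a correction for clustering.

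**The concern.** In their standard form, the chi-square test and logistic regression treat each woman as an independent observation. Women in one village share network coverage, distance to care and local norms, so their phone use and willingness are likely to be alike. The protocol itself expects villages to differ: it bands them by distance and plans to compare respondents between villages.

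Where a factor also varies between villages, the number of villages limits the information more than the number of women does. The ordinary standard error misses this. The Discussion says that the factors found will guide the tailoring of programmes in Thatta and elsewhere in Pakistan. A false association with a village-level factor would feed into that use.

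**Working it through.** **The plan's own figure.** The sample size starts from "we assumed that 50% of women use mobile phone and are willing to receive voice-message based mHealth intervention" and continues: "The maximum sample size is 384, which was calculated using the proportion of women who have mobile phone". For one proportion, n = z²p(1−p)/d² with z = 1.96, p = 0.5 and d = 0.05 (d is not stated and is assumed here). This gives 3.8416 × 0.25 / 0.0025 = 384.16, which reproduces 384. It is the simple-random-sample formula with no design effect, so clustering is absent from the sample size as well as from the analysis.

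**Inputs from the article.** 415 women, 20 villages, one woman per household, significance level 0.05 (taken as two-sided). Mean cluster size m = 415/20 = 20.75.

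**Assumed input.** ICC of the outcome within villages: 0.02, 0.05 and 0.10.

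**A prevalence or a purely village-level factor.**
- Design effect DE = 1 + (m − 1) × ICC = 1 + 19.75 × ICC.
- True SE / ordinary SE = √DE. Effective N = 415/DE.
- Actual coverage of a nominal 95% interval = 2Φ(1.96/√DE) − 1.
- Actual type I error of a single-parameter test = 2(1 − Φ(1.96/√DE)).
- For three distance bands (2 df, critical value 5.991), actual type I error ≈ exp(−2.996/DE).

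| ICC | DE | SE ratio | Effective N | Coverage | Type I, one parameter | Type I, three bands |
|---|---|---|---|---|---|---|
| 0.02 | 1.40 | 1.18 | 298 | 0.90 | 0.097 | 0.117 |
| 0.05 | 1.99 | 1.41 | 209 | 0.84 | 0.164 | 0.222 |
| 0.10 | 2.98 | 1.72 | 140 | 0.74 | 0.256 | 0.365 |

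For a prevalence near 50%, the ordinary half-width is 1.96 × √(0.25/415) = 4.8 points. Multiplied by √DE it becomes 5.7, 6.8 and 8.3 points.

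**Simulation check (20 villages, 415 women, no true effect, 4,000 runs each).** A beta-binomial simulation of the three-band chi-square rejected 0.108, 0.228 and 0.367 of the time. An ordinary Wald logistic test of a binary village-level factor rejected 0.087, 0.147 and 0.223 of the time at ICC 0.02, 0.05 and 0.10. Here the ICC is on the latent logistic scale, which corresponds to a smaller ICC on the outcome scale, so rates below the table are expected. At ICC 0.10 the mean model SE was 0.198 against a true SD of 0.320.

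**A factor that only partly clusters.** DE = 1 + (m − 1) × ICC(outcome) × ICC(factor). With a factor ICC of 0.10:
- outcome ICC 0.05: DE = 1 + 19.75 × 0.005 = 1.10, type I error 0.061;
- outcome ICC 0.10: DE = 1 + 19.75 × 0.010 = 1.20, type I error 0.073.

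The logistic simulation, with both ICCs on the latent scale, gave 0.054 and 0.055, so the inflation here is small at most.

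**A factor unrelated to village.** DE is about 1. The simulated type I error at latent-scale ICC from 0.02 to 0.20 was 0.046 to 0.052, which is in effect nominal.

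**The case against.** The strongest reply is that most of the planned analysis is not much harmed. Five of the six adjustment variables are attributes of the woman, and a factor balanced within villages keeps its 5% error rate. This stands. A reader might infer that every standard error and p-value in the study will be too small, but the design and the calculations do not support that.

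The highest rates, 11% to 37%, belong to a comparison of the three distance bands. The bands appear under Study setting, but distance is not among the variables listed under Data analysis. Those rates hold only if distance is tested, or if residence is coded that way. The coverage figures likewise apply only if an interval for a prevalence is reported. The stated descriptive plan is frequencies, means and SDs.

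If residence meant 20 village indicators, the adjusted model would absorb much of the clustering. The article does not say so, and the chi-square tests and unadjusted models would still be exposed. The planned comparison between villages uses village as the factor of interest and is not harmed in this way.

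The two stated objectives are descriptive, and ignoring the clustering in the analysis does not in itself bias their point estimates. That lowers the weight of the point.

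Finally, the article is condensed, and a fuller plan might specify clustered variance. But the article does fix the tests, software, significance level and covariates, and as written these do not match its sampling design.

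Purposive selection is no defence. It limits generalisation, but it does not make neighbours independent.

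**Conclusion.** The point holds within limits. As written, the analysis overstates precision for factors that vary by village and for any prevalence interval. For an assumed ICC of 0.02 to 0.10, the design effect is 1.4 to 3.0. The type I error of a nominal 5% single-parameter test of a village-level factor is about 10% to 26%. For partly clustered factors such as literacy or ownership it is about 6% to 7% if their own village ICC is 0.10 and the outcome ICC is 0.05 to 0.10. For factors balanced within villages there is almost no effect.

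The sizes rest on the assumed ICC, on roughly equal village samples and on a two-sided test. The direction rests only on some positive within-village correlation. A reader might go further and conclude that the study's main results would be invalid. The documents do not support that, because the factor analysis is secondary to the descriptive objectives. The point is worth correcting before analysis but is not a critical flaw.

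**What to change.** In Data analysis, replace the plain tests with a model-based clustered analysis:

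- Use GEE logistic regression with village as the cluster, or logistic regression with a village random intercept, for both unadjusted and adjusted odds ratios.
- Apply a small-sample correction suited to 20 clusters. If the named software version does not offer one, run these models elsewhere.
- Enter distance band as a covariate, and define residence.
- Give cluster-adjusted 95% confidence intervals for any prevalence reported.

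Rao-Scott tests or a complex-samples procedure should not be relied on as design-based inference. They presume probability selection, whereas villages and women are both chosen purposively.

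The change needs no new fieldwork. It needs village recorded for each woman, which the planned comparison between villages already requires. The costs are wider intervals and slightly more analysis work. It does not restore lost precision: on the assumed range, 415 women carry the information of about 298 down to 140 for a prevalence or a village-level contrast.

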## Discussion

This research project will provide invaluable information on the current access, usage of mobile phones among women of district Thatta and their willingness to receive voice messages to improve the antenatal care services. The study will also highlight demographic, sociocultural and economic factors associated with women willingness and readiness to receive voice messages regarding antenatal care. These insights will guide researchers on how mHealth programs can be tailored to local context, through developing cultural-sensitive messages in local languages, and following societal norms (sending messages on specific time of the day), to ensure successful implementation of such programs. These insights will support decisions on introducing tailored mHealth programs in Thatta and other parts of Pakistan to improve the antenatal care services. While mHealth programs has been proven effective for various chronic diseases and public health issues, it is a novel idea for supporting pregnant individuals for preventative maternal healthcare services, with very few previous studies in area. In this study, if willingness among women is captured towards mHealth intervention, our team will work to implement voice message-based mHealth intervention to improve ANC attendance among women of district.

